### Randomization method

Block randomization by study site will be employed, using a computer-generated list. Treatment allocation will be kept in sequentially numbered, sealed, opaque envelopes, which will be drawn for each randomized participant. We will retain all envelopes and records for quality-monitoring purposes.

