### Sample size calculations

We will enroll a total of 130 patients. This sample size was calculated as follows. A 1:1 ratio of patients will be assigned to SPO2 or control (cylinder O_2_). We consider a 1-day prolongation of hospital stay to be clinically significant (noninferiority margin). Using pilot data from a prospective study at Jinja Regional Referral Hospital, 69 patients with hypoxic pneumonia had a mean (standard deviation) length of stay of 2.6 (2.1) days (unpublished data). By standard calculations for normally distributed data, 57 patients in each group will provide 80 % power to demonstrate noninferiority of SPO2 relative to oxygen by cylinder at α = 0.05 (one-sided). This sample size was increased by 15 % to account for a probable non-Gaussian distribution of the data [12].

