### Primary analysis

Length of stay (in days) will be coded as a whole number (continuous variable). Difference in length of stay between groups will be compared using the nonparametric method of Hodges and Lehman. If the *a priori* noninferiority margin (Δ = 1 day) is below the lower limit of the 95 % confidence interval for the median of differences, the trial will conclude that SPO2 is noninferior to cylinder oxygen. In order to account for all patients randomized (“intention-to-treat” analysis), we will perform sensitivity analyses to account for missing data due to mortality, study withdrawal, and transfer to another facility. A *per protocol* population (non-fatal cases discharged home from hospital) will be used to assess the robustness of the primary result (non-inferiority). Details of the sensitivity analyses will be included in a Statistical Analysis Plan, which will be closed as early as possible in the conduct of the trial.

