### Secondary outcomes

The mortality will be compared between groups using the chi-squared statistic, or Fisher’s exact test, as appropriate. The proportion of patients successfully oxygenated and proportion of patients for whom the oxygen delivery system failed will be analyzed in a similar manner. The duration of oxygen therapy will be compared using nonparametric methods (Mann-Whitney U-test) and/or Cox-proportional hazard models. Costs will be carefully tabulated (capital investment, ongoing costs, and system maintenance, *etcetera*) and summarized for each group of patients. Details of maintenance needs and convenience of use of the systems will be documented and tabulated. The LODS and RISC (clinical severity scores) will be assessed and recorded serially over the course of hospital admission; comparison between groups will make use of linear mixed effects models to compare the longitudinal time course of the clinical severity score during convalescence.

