Several potential confounding factors may impact our primary outcome (length of stay) or secondary outcomes (for example, mortality) among patients with hypoxemia. These include host factors (for example, patient age, underlying immune deficiency like HIV), disease-specific factors (for example, pathogen and severity of infection), and co-treatments (for example, antibiotics). Our randomized design is expected to distribute these variables equally between study arms, and we have not attempted to stratify the cohort due to the modest sample size. Secondary analyses (for example, multivariable regression) may be undertaken to explore the important predictors of patient outcomes in this cohort.

Potential impacts of solar-powered oxygen delivery include a reduction in pneumonia-specific and overall child mortality if this technology can be brought to scale and implemented widely in Africa and Asia. Toward this goal, our RCT will provide strong empirical data to support the feasibility and noninferiority of SPO2 in resource-limited African hospitals. We anticipate that this trial will also provide valuable data for future design and refinement of solar-powered oxygen delivery systems, including the potential for commercial development. A significant reduction in the number of children dying of pneumonia may be realized with this pragmatic method to provide supportive therapy with oxygen globally.

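### Randomization is blocked by site, but the primary Hodges-Lehmann comparison pools the two sites; the result is valid but less precise than it could be if stay differs between hospitals

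*Protocol article*

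**What the plan says.** Under Randomization method the protocol states: "Block randomization by study site will be employed, using a computer-generated list". Blocking within site is stratification by site.

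Under Primary analysis it states: "Difference in length of stay between groups will be compared using the nonparametric method of Hodges and Lehman". Stay is coded in whole days, and no site stratum or covariate is named. That section leaves only the details of the sensitivity analyses to the statistical analysis plan.

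Under Sample size calculations the variability comes from a pilot at Jinja only, where "69 patients with hypoxic pneumonia had a mean (standard deviation) length of stay of 2.6 (2.1) days". From this the protocol concludes that "57 patients in each group will provide 80 % power to demonstrate noninferiority" at a one-sided 5% level with a margin of 1 day. It then adds 15% for non-normality and arrives at 130 children.

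Under Secondary outcomes, "The LODS and RISC (clinical severity scores) will be assessed and recorded serially over the course of hospital admission", but the scores serve only as outcomes. The Discussion lists host factors, disease factors (including severity) and co-treatments as possible influences on stay, relies on randomization to balance them, and says "we have not attempted to stratify the cohort due to the modest sample size". Multivariable regression is an optional exploratory analysis.

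**The concern.** When allocation is balanced within site, the difference between arms is free of site-to-site variation by design. A pooled two-sample rank analysis does not know this: it treats any difference in stay between hospitals as random noise. The interval is then wider than the design requires, and the noninferiority test rejects less often than its nominal level allows.

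A site difference is plausible. Study setting contrasts a referral hospital with a large catchment and a remote hospital with limited road access. The sample size cannot have allowed for it, because its only SD comes from one of the two hospitals. What is at stake is some power to show noninferiority, not the validity of the conclusion.

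**Working it through.** **Inputs from the protocol.** Margin 1 day, SD 2.1 days (Jinja), one-sided α 0.05, power 80%, 57 per group before inflation, 130 in total, so 65 per arm.

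**Assumed, because the documents give no figure.** Site gap d from 0 to 2 days; 70% of children from one site and 30% from the other; SD 2.1 within each site.

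**1. The plan's own figure.** n = 2 × SD² × (z₀.₉₅ + z₀.₈₀)² / margin² = 2 × 4.41 × (1.645 + 0.842)² / 1 = 54.5, so 55 per group. A t-based calculation gives 56, and dividing 54.5 by the Wilcoxon efficiency of 0.955 gives 57.1. The stated 57 is reproduced closely. With inflation, 57 × 1.15 = 65.6 per group, or 131 in total, against 130 stated.

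**2. Pooled SD with a site gap.** SD_pooled = √(2.1² + 0.7 × 0.3 × d²) = √(4.41 + 0.21 d²).

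**3. Half-width and power at 65 per arm.** SE = SD × √(2/65); half-width = 1.645 × SE; power = Φ(1/SE − 1.645).

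| Site gap (days) | Pooled SD | Half-width (days) | Power, pooled | Power, site accounted for |
|---|---|---|---|---|
| 0 | 2.100 | 0.606 | 85.8% | 85.8% |
| 0.5 | 2.112 | 0.610 | 85.4% | 85.8% |
| 1 | 2.149 | 0.620 | 84.3% | 85.8% |
| 1.5 | 2.210 | 0.638 | 82.5% | 85.8% |
| 2 | 2.291 | 0.661 | 80.0% | 85.8% |

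The half-width is 0.606 throughout when site is accounted for. So the pooled interval is about 2% wider at a 1-day gap (0.620/0.606) and about 9% wider at 2 days (0.661/0.606). Under a 50/50 split, pooled power is 84.0% at 1 day and 79.0% at 2 days. Under 80/20 it is 84.7% and 81.4%.

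**4. Check with a rank test on whole days.** Simulation of 4,000 trials per scenario: gamma-distributed stay with mean 2.6 and SD 2.1, rounded up to whole days, equal sites. Power of the pooled against the site-stratified rank test, one-sided 5%:
- no gap: 95.6% against 95.6%
- 1-day gap: 94.0% against 96.0%
- 2-day gap: 89.0% against 95.9%

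The direction agrees with step 3. Both levels are higher because a rank method is more efficient on skewed data. Stratifying costs nothing when the sites are alike.

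**5. Baseline covariates.** On normal theory, adjustment narrows the interval by 1 − √(1 − R²). For an assumed R² of 10% this is 1 − √0.90 = 5%; for 20% it is 1 − √0.80 = 11%. The documents give no R².

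**The case against.** **The pooled analysis is valid.** This stands. Ignoring the blocking is conservative for a noninferiority claim. It causes neither bias nor an excess of false claims.

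**The size is not in the documents.** This also stands. If the sites do not differ, nothing is lost. A 2-day gap is extreme against a pilot mean of 2.6 days, and the common discharge rule works against one. At 1 day the loss is about 1.5 power points.

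**Whole-day coding may swallow the gain.** Partly. In a simulation with stays rounded up, the pooled and site-aligned intervals were identical in 81–88% of trials for gaps of 0 to 1 day, and in 66% at 2 days. But limits that move in whole-day steps can also jump onto the margin. If the upper limit must lie strictly below 1 day (assumed 45/20 split per arm), power pooled against aligned was 54% against 57% with no gap, 48% against 58% at 1 day and 41% against 60% at 2 days. About 3 points of that difference come from the alignment itself, not from site. The gain therefore depends on how a limit equal to the margin is treated, and I do not rely on these figures for the size.

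**Adjustment is commonly left to the analysis plan, which is not shown.** For patient covariates this is fair, so that part is only a suggestion. For site it is weaker: Primary analysis names the method itself and defers only the sensitivity analyses.

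**Stronger readings that a reader might infer, and that are not supported:**
- *That the Discussion contradicts the randomization section.* The sentence containing "we have not attempted to stratify the cohort due to the modest sample size" concerns host, disease and co-treatment factors. Site is not among them, so it is compatible with blocking by site.
- *That the trial falls below its planned power.* A drop from 82% to 75% appears at 57 per arm with a 2-day gap, but the trial enrolls 65 per arm. There the 70/30 case still reaches 80.0%.
- *That a known baseline severity score is being wasted.* Serial recording implies an admission value, but the protocol does not state one, nor how strongly it predicts stay.

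**Conclusion.** The point holds as a matter of efficiency. The design balances the arms within site, and the primary comparison as written does not use this. The interval is wider than needed if, and only if, stay differs between the hospitals. Under the protocol's SD, 65 per arm, one-sided 5% and an assumed 70/30 split, the loss on the planning formula is nil with no gap, about 1.5 power points at 1 day and about 6 points at 2 days. Only the upper end of that range is material, and it rests on a gap that nothing in the documents supports. Even there power stays at about the planned 80%, falling just short, at 79.0%, only under an equal split. This is a modest improvement that costs almost nothing; it does not correct an invalid analysis.

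**What to change.** Make a site-stratified (site-aligned) Hodges-Lehmann estimate and interval the primary analysis, and keep the pooled version as a sensitivity analysis. Recruitment is under way and the protocol describes the statistical analysis plan as still to be closed, so the change can be made before analysis. It needs a sentence in the plan and a few lines of code. No new data are required, and there is essentially no loss of precision if the sites are alike.

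Optionally, prespecify a supportive analysis adjusted also for age, admission saturation and the first LODS or RISC score, provided that score is recorded before treatment. Its gain depends on how prognostic these are.

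In the Discussion, a short clarification that the absence of stratification refers to patient factors, and that randomization was blocked by site, would prevent a misreading.

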### Study objectives

The overall objective is to demonstrate the noninferiority of solar-powered oxygen delivery relative to standard oxygen delivery. Specifically, we will compare the length of stay in children hospitalized with acute hypoxic respiratory illness randomized to SPO2 versus cylinder oxygen. The working hypothesis is that the length of stay is not increased in children treated with SPO2 compared to children receiving cylinder oxygen. Secondary outcomes will be compared between groups, including patient-specific outcomes (mortality, duration of supplemental oxygen therapy (time to wean O_2_), proportion of patients successfully oxygenated, and clinical severity scores) and oxygen delivery system indicators (system failures, cost, maintenance and convenience of use).

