Noteworthy aspects of this trial include its setting in two severely resource-limited hospitals, where hypoxemic patients do not have reliable access to oxygen, intensive care environment, endotracheal intubation, or mechanical ventilatory support. This situation is common across hospitals in sub-Saharan Africa [5], and contributes to elevated mortality rates from pediatric pneumonia. Threats to consistent oxygen supply in our centers and others include weak supply chain for oxygen cylinders, inconsistent electric power supply, and lack of well-maintained oxygen concentrators. The use of solar-powered oxygen eliminates the need for oxygen cylinders and electricity but will still require minimal equipment maintenance. The study setting in equatorial Uganda is also representative of many African sites, where solar energy is abundant and can be harnessed for oxygen purification from ambient air. Our trial will provide “real-life” data on system operation under field conditions including variability in sun intensity throughout the day and with weather conditions (energy available) and patient oxygen demands. These features increase the generalizability of our findings to similar settings and will inform future refinements and optimization of the solar-powered oxygen delivery system.

One limitation of this study is the lack of blinding. Given the nature of the intervention (oxygen concentrator or cylinder), it is not feasible to blind clinicians or participants to the intervention in our setting. Decisions about the primary outcome (length of stay) are subject to clinician judgment, opening the possibility of bias. To mitigate this potential bias, we will use objective criteria for hospital discharge, which will be applied uniformly to patients in both arms. We have chosen length of stay (continuous variable), rather than mortality as the primary study endpoint for pragmatic reasons. The binary outcome mortality would require a much larger and costlier study to show noninferiority (sample size of n = 1,134 per group needed to show noninferiority within a margin of 5 % absolute risk difference). For the sample size calculation, we used a one-sided 5 % significance level, rather than the more conventional two-sided approach. This reduced the total sample size by approximately 30 patients while still permitting demonstration of noninferiority with 95 % confidence (based on the lower limit of the one-sided confidence interval).

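### The noninferiority rule is reversed: as printed, it passes SPO2 only when the whole confidence interval lies above +1 day

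*Protocol article*

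**What the plan says.** Two sections of the protocol article fix the direction of harm. Study objectives: "The working hypothesis is that the length of stay is not increased in children treated with SPO2 compared to children receiving cylinder oxygen". Sample size calculations: "We consider a 1-day prolongation of hospital stay to be clinically significant (noninferiority margin". A longer stay on SPO2 is therefore the bad outcome, and one extra day is the boundary.

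The Primary analysis section then gives the decision rule. The condition is that the "noninferiority margin (Δ = 1 day) is below the lower limit of the 95 % confidence interval for the median of differences"; the operative words are "is below the lower limit of the". If it is met, "the trial will conclude that SPO2 is noninferior to cylinder oxygen".

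The order of subtraction is not stated. The same section says only: "Difference in length of stay between groups will be compared using the nonparametric method of Hodges and Lehman". The Discussion, explaining the choice of a one-sided 5% level, again names the lower bound: "based on the lower limit of the one-sided confidence interval".

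**The concern.** If the margin of +1 day lies below the lower limit, the whole interval lies above +1 day. For a difference taken as SPO2 minus cylinder, that result demonstrates inferiority, yet the protocol attaches the conclusion of noninferiority to it.

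This is the only rule that turns the primary data into the trial's conclusion. The trial is open-label, and the Discussion concedes that the primary outcome depends partly on clinician judgment, so the direction of the test should not have to be interpreted after the data are seen. The Primary analysis section leaves only the details of the sensitivity analyses to the SAP. The decision rule is fixed in the protocol, and an SAP that stated it correctly would contradict the published text.

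**Working it through.** **Inputs.** From Sample size calculations: margin 1 day, SD 2.1 days, 57 per group, 80% power, one-sided α = 0.05, 15% inflation, total 130 at 1:1 (65 per arm). From Study objectives: a longer stay is worse.

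**1. The plan's own sample size.** With no true difference,

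n per group = 2 × [2.1 × (1.645 + 0.842)]² / 1² = 54.5, so 55.

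A t-based calculation gives 55.2, so 56. The plan states 57, which is close enough. Inflation: 114 × 1.15 = 131, against 130 stated. A one-sided 0.025 level needs 70 per group, which is 2 × (70 − 55) = 30 more patients and matches the saving of about 30 given in the Discussion. These figures all presuppose the conventional rule, in which the limit on the harmful side must stay inside the margin.

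**2. The printed rule under each order of subtraction.**

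- SPO2 minus cylinder: lower limit > +1 means SPO2 is shown to prolong stay by more than 1 day. A noninferiority test needs upper limit < +1.
- Cylinder minus SPO2: lower limit > +1 means SPO2 is shown to shorten stay by more than 1 day. A noninferiority test needs lower limit > −1.

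The printed rule matches neither requirement.

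**3. Probability of declaring noninferiority.** Normal approximation, 65 per arm, one-sided 95% limit, with d the true difference SPO2 minus cylinder:

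- SE = 2.1 × √(2/65) = 0.368, and 1.645 × SE = 0.606
- Printed rule, SPO2 minus cylinder: 1 − Φ((1.606 − d)/0.368)
- Printed rule, cylinder minus SPO2: 1 − Φ((1.606 + d)/0.368)
- Conventional rule: Φ((0.394 − d)/0.368)

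| True d (days) | Printed, SPO2 − cylinder | Printed, cylinder − SPO2 | Conventional |
|---|---|---|---|
| −1 | <0.00001 | 0.050 | 0.9999 |
| 0 | 0.0000065 | 0.0000065 | 0.858 |
| +1 | 0.050 | <0.00001 | 0.050 |
| +1.5 | 0.387 | <0.00001 | 0.001 |
| +2 | 0.858 | <0.00001 | <0.0001 |

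With 57 per group the conventional rule gives 0.815 at d = 0, in line with the stated 80%. The printed rule is nowhere near 80% at d = 0 under either order.

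**4. Sensitivity to the interval.** With a two-sided 95% interval and 65 per arm, the printed rule (SPO2 minus cylinder) gives <0.00001 at d = 0, 0.025 at +1 and 0.775 at +2. The reversal does not depend on sidedness.

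**5. Sensitivity to the method.** The planned analysis is a Hodges-Lehmann interval on whole-day data, so it was also simulated: 2,000 trials per scenario, 65 per arm, gamma stays with mean 2.6 and SD 2.1 rounded up to whole days (the gamma shape and the rounding are assumptions), one-sided 95% limit. The printed rule passed 0% at d = 0, 56.5% at +2 and 99.95% at +3. The rule upper limit < 1 passed 56.2% at d = 0 and 0% at +2. The levels differ from the normal approximation because limits computed from whole-day data fall on whole days. The direction of the error is the same.

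**The case against.** The strongest defence is that this is a slip of sign and not inverted logic. Both the Primary analysis and the Discussion name the lower limit, which is the right limit if the difference is cylinder minus SPO2 and the margin is −1 day. Δ = 1 day could then be a magnitude printed without its sign. On that reading the Discussion sentence is not wrong in itself, because it gives neither a sign nor a direction. The intent is also plain from the objectives, the definition of the margin and the sample size, so a competent analyst would probably apply the right rule. Finally, the statement that the printed rule favours a harmful device holds only for SPO2 minus cylinder. With the other order it is far too strict.

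The slip is a plausible origin, and the Discussion needs alignment only. But the defence needs a minus sign and an order of subtraction that the document nowhere supplies. With the margin as printed, the rule fails under both orders, and describing the margin as a prolongation points to SPO2 minus cylinder, the order under which the rule rewards harm. Clear intent elsewhere makes the error easy to correct; it does not make the printed rule usable.

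**Conclusion.** The rule is wrong as written and must be corrected. It contradicts the hypothesis, the definition of the margin and the stated power. Read literally as SPO2 minus cylinder, it almost never passes a device that is truly equivalent (about 0.0007%), passes one that adds 1.5 days 39% of the time, and passes one that adds 2 days 86% of the time. The conventional rule gives about 86% at no difference with 65 per arm (81.5% with 57) and 5% at the margin.

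These figures assume SD 2.1 in both arms, 65 analysed per arm, a one-sided 95% limit and a normal approximation. They show the direction and rough size of the error and are not a power statement for the Hodges-Lehmann analysis. That the printed rule is not a noninferiority test follows from its wording alone and needs none of these assumptions. The sample size is not affected.

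**What to change.** Replace the rule in the Primary analysis section with, for example: *The difference is defined as SPO2 minus cylinder in length of stay. SPO2 is noninferior if the upper one-sided 95% confidence limit for the Hodges-Lehmann shift (the upper limit of the two-sided 90% interval) is below +1 day.* The one-sided level is the one already used in Sample size calculations and the Discussion; the rule should name it, because the Primary analysis section now says only 95%. In the Discussion, change the lower limit to the upper limit.

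An equivalent correction is to define the difference as cylinder minus SPO2 and require the lower one-sided 95% limit to be above −1 day, in which case the Discussion wording can stay. Either is sound, but one must be chosen and the SAP must match it.

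The cost is one sentence in the protocol and SAP and, with the first option, one word in the Discussion. Sample size, data collection and conduct are unchanged. Recruitment was ongoing at publication, so the correction should be made and dated before any comparison of the arms.

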### Outcome measures

Length of stay will be the primary outcome. A standardized and objective decision rule will be used for hospital discharge. All of the following criteria will be required for discharge: (1) off oxygen for at least 24 hours (requires saturation ≥90 % on room air); (2) absence of fever for 24 hours; (3) vital signs stable; and (4) drinking and/or breastfeeding well.

Several secondary outcomes will be recorded. Patient-specific outcomes will be measured in each group: mortality, proportion of patients successfully oxygenated, duration of oxygen therapy, and clinical severity score. The proportion of patients successfully oxygenated will be defined as the number of patients who achieve a saturation ≥90 % for ≥12 hours after initiating oxygen therapy. The clinical severity scores used will be the previously published and validated Lambaréné Organ Dysfunction Score (LODS) [10] and the Respiratory Index of Severity in Children (RISC) [11].

Oxygen delivery system variables will include direct costs (capital investment, operating costs, system maintenance, *etcetera*), details of maintenance needs, convenience of use of the systems and proportion of patients for whom the delivery system failed. System failure will be defined as inadequate oxygen production to meet patient needs for any reason. Examples would include battery failure for SPO2 or out-of-stock cylinder oxygen.

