### Safety

Oxygen therapy is known to be a life-saving intervention, and this study will improve hospital capacity for the treatment of hypoxemic children. While patients will be randomized to one of two possible oxygen delivery systems, there are no risks, and benefits include potentially life-saving access to oxygen, regardless of delivery modality. Study participants will be managed at the Jinja Regional Referral Hospital according to national guidelines and local clinical practices. Outcome assessment in the study will not pose any risk to the study participants.

Adverse events, defined according to Good Clinical Practice (GCP) guidelines as any untoward event occurring in a study participant, will be logged prospectively and tabulated at the end of the study, disaggregated by study arm. Severe adverse events, defined as those adverse events that prolong hospitalization or lead to permanent disability or death, will be reported to regulatory authorities in an expedited manner and reported separately in the safety analysis.

This study involves hypoxemic patients with severe pneumonia or very severe disease, and the mortality is expected to be high because of the underlying illness. Mortality among patients receiving SPO2 will to be interpreted in comparison to patients receiving O_2_ by standard method (cylinders).

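### Death is classed as missing length-of-stay data, and the noninferiority conclusion rests on length of stay alone, so excess deaths in one arm need not count against it

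*Protocol article*

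**What the plan says.** All references are to the protocol article; the statistical analysis plan is not shown.

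- Outcome measures: "Length of stay will be the primary outcome". The discharge rule is strict: "All of the following criteria will be required for discharge", and the list covers oxygen, fever, vital signs and feeding.
- Primary analysis: the stay is coded in whole days and compared by the Hodges-Lehmann method. If the confidence limit is on the right side of 1 day, "the trial will conclude that SPO2 is noninferior to cylinder oxygen". No condition on mortality is attached.
- Primary analysis, on incomplete outcomes: under an intention-to-treat label, it plans "sensitivity analyses to account for missing data due to mortality, study withdrawal, and transfer to another facility", with details deferred to the SAP. A per protocol "population (non-fatal cases discharged home from hospital) will be used to assess the robustness of the primary result".
- Safety: "the mortality is expected to be high because of the underlying illness". No rate is given.
- Secondary outcomes: mortality is compared between arms by a chi-squared or Fisher test, with no margin and no stated link to the primary conclusion.
- Discussion: showing noninferiority on mortality would need 1,134 per group.

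**The concern.** Withdrawal and transfer leave the length of stay unobserved. Death does not. The stay serves as a measure of time to recovery, and a child who dies is known never to have recovered. Placing death beside withdrawal and transfer treats the worst result in the trial as absent information.

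The direction of the effect matters. Excluding fatal cases removes the arm's worst results from the comparison. Entering time to death as a stay turns an early death into a short, favourable value. The named robustness population, "non-fatal cases discharged home from hospital", is itself defined by an outcome that arises after randomization and may depend on oxygen delivery. In a noninferiority trial these choices favour the conclusion the trial hopes to reach. The article expects high mortality and anticipates delivery failures in either arm, so a difference in deaths is a practical possibility.

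**Working it through.** **1. Inputs.** From Sample size calculations: mean stay 2.6 days, SD 2.1, margin 1 day, one-sided α = 0.05, power 80%, 57 per group, raised 15% "to account for a probable non-Gaussian distribution of the data", total 130 (65 per arm). Assumed: the mortality rates, and gamma or lognormal stays with that mean and SD.

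**2. The plan's own figure.** n per group = 2(1.645 + 0.842)² × 2.1² / 1² = 2 × 6.19 × 4.41 ≈ 54.6, so 55; the noncentral-t version gives 56. The stated 57 is within two patients. 57 × 1.15 × 2 = 131.1, against 130 stated. The sample size is reproduced.

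**3. Simulation.** 65 per arm, 1,500 trials per row, stays drawn from the same distribution in both arms, deaths independent of stay. Noninferiority is declared when the one-sided 95% Hodges-Lehmann limit for excess stay on SPO2 is below 1 day. (The article words its rule with the lower limit; the limit used here is the one that bears on prolongation.) Deaths are excluded, entered as stays of 0–1 day, or ranked worst. Entries are the percentage of trials declaring noninferiority.

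| Stays | Mortality, cylinder / SPO2 | Excluded | 0–1 day | Worst rank |
|---|---|---|---|---|
| Gamma, continuous | none | 96.3 | 96.3 | 96.3 |
| | 10% / 10% | 94.2 | 95.9 | 87.3 |
| | 10% / 20% | 92.5 | 99.9 | 47.3 |
| | 15% / 30% | 89.5 | 99.9 | 24.5 |
| Lognormal, continuous | none | 99.1 | 99.1 | 99.1 |
| | 10% / 10% | 98.3 | 98.9 | 95.5 |
| | 10% / 20% | 97.8 | 100.0 | 64.4 |
| | 15% / 30% | 96.5 | 99.9 | 35.6 |
| Gamma, whole days | none | 51.3 | 51.3 | 51.3 |
| | 10% / 10% | 47.2 | 51.7 | 42.6 |
| | 10% / 20% | 46.5 | 79.7 | 10.9 |
| | 15% / 30% | 46.3 | 91.9 | 5.0 |
| Lognormal, whole days | none | 71.0 | 71.0 | 71.0 |
| | 10% / 10% | 63.8 | 65.4 | 57.1 |
| | 10% / 20% | 61.0 | 88.1 | 17.9 |
| | 15% / 30% | 60.9 | 96.0 | 7.8 |

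The simulation standard error near 50% is √(0.25/1500) ≈ 1.3 points. A separate simulation of the 10% / 20% case gave 91–98% (excluded) against 48–65% (worst rank) in continuous days, and 42–59% against 11–18% in whole days. The two agree to within a few points.

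Whole-day figures are lower throughout because differences between whole numbers are whole numbers: a limit below 1 must be 0 or less.

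With the limit of a two-sided 95% interval instead, the 10% / 20% case gives 86–95% against 36–52% (continuous) and 36–49% against 8–11% (whole days). The pattern does not depend on that choice.

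**4. The mortality test as a safeguard.** With 65 per arm and two-sided 0.05, exact power to detect 10% against 20% is 28% (Fisher) to 35% (uncorrected chi-squared). For 5% against 10% it is 10–19%, and for 15% against 30% it is 46–54%. Reaching 80% power for 10% against 20% needs 199 per arm.

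**5. When SPO2 truly prolongs stay by 1 day** (gamma, continuous days only). With deaths independent of stay at 10% / 20%, noninferiority is wrongly declared in 5.9% of trials with deaths excluded, 36.3% with deaths as short stays and 1.0% with worst rank; without deaths it is 5.1%. If deaths concentrate in longer stays, exclusion gives about 10–11% and worst rank about 1%, with either distribution. In whole days the rate is at most about 2% under any handling.

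**The case against.** The strongest reply has four parts.

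First, the article plans intention-to-treat sensitivity analyses for deaths and defers their method to an SAP, which may use worst ranks. A reader might infer that the only robustness check is in survivors. That is not so, and the deferred detail is not a fault. What remains is that the article itself labels death as missing and assigns it to sensitivity analyses, which are not stated to constrain the conclusion.

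Second, the article does not say whether the primary analysis drops deaths or counts time to death. This is correct. The exclusion and short-stay columns show what each reading would do; neither is a stated rule.

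Third, a reader might take the 91–98% as inflation caused by excluding deaths. It is not: with no deaths at all, 96–99% of trials pass, because stays are equal in survivors. The figure shows a conclusion that ignores deaths. It is not a raised error rate for stay among survivors, which remains near 5% when deaths are unrelated to stay. The excess in step 5 is a continuous-day result and largely disappears with the planned coding.

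Fourth, length of stay was chosen openly over mortality for feasibility, and mortality will be reported by arm. That stands, but the mortality test usually misses a doubling and cannot alter the primary conclusion.

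A reader might also infer that, because the 15% inflation is reserved for non-normality, excluding deaths brings power below the planned 80%. The simulation of the planned method does not support this. With 10% of each arm excluded, it moves from 96% to 94% (gamma) or 99% to 98% (lognormal) in continuous days. The much lower whole-day figures come mainly from the coding and are present without any deaths.

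**Conclusion.** The concern holds in this form: the article classes a known unfavourable outcome as missing data, makes survival part of its named robustness population, and lets noninferiority be concluded from length of stay alone. At an assumed 10% against 20% mortality with equal stays in survivors, excluding deaths leaves a 91–98% chance of declaring noninferiority in continuous days, or 42–59% in whole days. Ranking deaths worst lowers this to 48–65% or 11–18%. The direction was the same for every mortality difference and both stay distributions examined. The size rests on the assumed mortality and distribution, on deaths independent of stay, and above all on the coding of days. The documents do not establish that the primary analysis will exclude or truncate deaths.

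**What to change.** State in the Primary analysis section, and carry into the SAP before it is closed:

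- The primary analysis includes all randomized children in their assigned arm. In-hospital death takes the worst rank, a value longer than any observed stay, in the Hodges-Lehmann comparison.
- Only withdrawal and transfer are treated as missing length of stay.
- The analysis of survivors discharged home is supportive.
- The mortality difference, with its confidence interval, is reported beside the noninferiority conclusion.

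Time to discharge alive, with death as a competing event, would be a defensible alternative; the essential step is to settle the handling of death in the primary analysis.

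The change is to wording and needs no new patients or data. Recruitment was still under way when the article was written, so the change should be made without reference to outcomes by arm. It has three costs. The estimate becomes a composite of death and longer stay. At equal 10% mortality, power falls from about 94% to 88% (gamma) or 98% to 95% (lognormal) in continuous days, and from about 46% to 41% or 62% to 56% in whole days. Worst ranking also reduces, but does not remove, the chance of declaring noninferiority despite excess deaths, which is why the mortality interval belongs beside the conclusion.
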